## Abstract

**Background:**

The presence of pulmonary hypertension (PH) severely aggravates the clinical course of heart failure with preserved ejection fraction (HFPEF) resulting in substantial morbidity and mortality. So far, neither established heart failure therapies nor pulmonary vasodilators have proven to be effective for this condition. Riociguat (Adempas®, BAY 63-2521), a stimulator of soluble guanylate cyclase, is a novel pulmonary and systemic vasodilator that has been approved for the treatment of precapillary forms of PH. With regard to postcapillary PH, the DILATE-1 study was a multicenter, double-blind, randomized, placebo-controlled single-dose study in subjects with PH associated with HFPEF. Although there was no significant change in the primary outcome measure, peak decrease in mean pulmonary artery pressure with riociguat versus placebo, riociguat significantly increased stroke volume without changing heart rate, pulmonary artery wedge pressure, transpulmonary pressure gradient or pulmonary vascular resistance. The present study is designed to test the efficacy of long-term treatment with riociguat in patients with PH associated with HFPEF.

**Methods/study design:**

The DYNAMIC study is a randomized, double-blind, placebo-controlled, parallel-group, multicenter clinical phase IIb trial evaluating the efficacy, safety and kinetics of riociguat in PH-HFPEF patients. The drug will be given over 26 weeks to evaluate the effects of riociguat versus placebo. The primary efficacy variable will be the change from baseline in cardiac output at rest, measured by right heart catheter after 26 weeks of study drug treatment. Additional efficacy variables will be changes from baseline in further hemodynamic parameters, changes in left and right atrial area, right ventricular volume, as well as right ventricular ejection fraction measured by cardiac magnetic resonance imaging, and changes from baseline in World Health Organization (WHO) class and N‑terminal prohormone B‑type natriuretic peptide (NT-proBNP).

The trial was registered on 25 August 2014 (EudraCT Number: 2014-003055-60; www.clinicaltrialsregister.eu).

## Background

Nearly half of the patients presenting with symptoms of heart failure have a normal left ventricular ejection fraction [1]. This condition is called heart failure with preserved ejection fraction (HFPEF) and also known as diastolic heart failure. The major determinant of mortality in this patient population is coexisting pulmonary hypertension (PH) [2], classified as group 2.2 in the Dana Point classification [3]. Despite the frequency and severity of HFPEF, effective medical treatment is lacking. sRiociguat (Adempas®, BAY 63-2521), an oral stimulator of soluble guanylate cyclase, is a novel pulmonary and systemic vasodilator that has been approved for precapillary forms of PH, e.g. chronic thromboembolic pulmonary hypertension (CTEPH) [4] and pulmonary arterial hypertension (PAH) [5]. Two phase II trials have indicated a potential benefit of riociguat treatment also in patients with postcapillary PH due to left heart disease. The phase IIb Left ventricular systolic dysfunction associated with pulmonary hypertension riociguat trial (LEPHT) study was a multicenter, double-blind, randomized, placebo-controlled study in subjects with PH resulting from heart failure with reduced ejection fraction (HFREF) [4, 6]. A total of 201 subjects were randomized to treatment with oral placebo or riociguat (0.5, 1 or 2 mg TID) for 16 weeks in 4 parallel arms. The primary outcome was the placebo-corrected change from baseline at week 16 in mean pulmonary artery pressure (PAPmean). Although the decrease in PAPmean in the riociguat 2 mg group was not significantly different from placebo, cardiac index and stroke volume index were significantly increased without changes in heart rate (HR) or systolic blood pressure (SBP) compared with placebo. Both pulmonary and systemic vascular resistance (PVR and SVR) were significantly reduced with 2 mg riociguat TID. Riociguat reduced the Minnesota Living with Heart Failure (MLHF) score.

The proof of concept study DILATE-1 was a multicenter, double-blind, randomized, placebo-controlled single-dose study in subjects with PH associated with HFPEF [7]. Clinically stable subjects with a left ventricular ejection fraction (LVEF) >50 %, PAPmean ≥25 mm Hg and pulmonary arterial wedge pressure (PAWP) >15 mm Hg at rest were randomized to single oral doses of placebo or riociguat. There were no significant changes in peak decrease in PAPmean with riociguat 2 mg versus placebo; however, riociguat 2 mg significantly increased stroke volume and decreased SBP and right ventricular end-diastolic area, without significantly changing HR, PAWP, the transpulmonary pressure gradient (TPG) and PVR. Based on the results of the single-dose DILATE-1 study in PH-HFPEF patients and the LEPHT study over 16 weeks in subjects with PH-HFREF, the present study is expected to generate data to assess the therapeutic potential of riociguat in PH-HFPEF.

## Study design

The DYNAMIC study is a randomized, double-blind, placebo-controlled, parallel-group, multicenter clinical phase IIb trial evaluating the hemodynamic effects, safety, and kinetics of riociguat in PH-HFPEF patients. The study drug will be administered over 26 weeks to evaluate the effects of riociguat versus placebo. Written informed consent will be obtained from patients in accordance with the Declaration of Helsinki and the ethics committee of the Medical University of Vienna has approved the study protocol (date of vote: 10-OCT-2014; reference number: EK 1570/2014).

## Titration and treatment phases

After a pretreatment phase of up to 4 weeks, the study phase will consist of an 8‑week (up-)titration phase followed by the 18-week fixed-dose treatment. Patients will be randomized to the active treatment arm or placebo. The starting dose of riociguat will be 0.5 mg 3 times a day (TID). At visits 2 and 3 (weeks 2 and 4), up-titration to a dose of 1.0 and 1.5 mg TID (Fig. 1) is based on clinical condition and systemic SBP, measured before intake of the next study drug dose in accordance with the following algorithm:

**Fig. 1 Fig1:**
[figure not shown]
Scheme of up-titration regimen in the DYNAMIC study. *TID* 3 times a day, *v* study visit. **a** up-titration of riociguat up to 1.5 mg TID. **b** sham titration placebo TID

During the titration phase in the first 8 weeks, the dose for the next titration step will depend on the SBP measured at trough before intake of the next study drug dose. The following algorithm applies to the individual dose titration (IDT) scheme:If trough SBP is ≥110 mm Hg, increase the dose.If trough SBP is between 100 and 109 mm Hg without symptoms of hypotension, maintain the dose.If trough SBP is <100 mm Hg without symptoms of hypotension, reduce the dose.

The IDT scheme is based on blood pressure and consideration of the subject’s clinical condition; therefore, in cases of poor tolerability, a planned up-titration step may be postponed and the dose maintained. During the 18-week treatment phase (from visit 3 to visit 6), all patients will receive the dose of visit 3. Dose reductions or interruptions for safety reasons are allowed at any time.

## Selected patient enrolment criteria

Eligible patients will be aged 18–80 years at the time of informed consent and have symptomatic PH-HFPEF, e.g. group 2/2.2 of the Dana Point classification [3] and World Health Organization (WHO) class II to IV, defined as:LVEF ≥50 %, diagnosed by echocardiography or left heart catheterization (LHC) within 30 days before randomization,PAPmean ≥25 mm Hg at rest, measured by right heart catheter (RHC) within 12 weeks before randomization,PAWP >15 mm Hg at rest, measured by RHC within 12 weeks before randomization.

The dose regimen of the background treatment must have been stable for >30 days before randomization. Diuretic therapy must have been stable for ≥1 week.

Selected exclusion criteria are listed in Table 1.

**Table 1 Tab1:** Selected exclusion criteria

Cardiac decompensation, either with hospitalization or visit to the emergency department ≤30 days before randomization
Resynchronization therapy
Need of IV diuretics ≤30 days before randomization
Treatment with IV inotropes or IV vasodilators ≤30 days before randomization
Chronic treatment with ERAs, PDE-5 inhibitors or prostanoids ≤30 days before randomization or with nitrates or PDE-5 inhibitors indicated for erectile dysfunction ≤7 days before randomization
Bronchial asthma or COPD with FEV_1_ <60 % of predicted
Restrictive lung disease with TLC <60 % of predicted
Current O_2_ therapy
Clinically relevant hepatic dysfunction indicated by either AST ≥3 times the upper limit of normal or Child-Pugh stage B and C in patients with cirrhosis
Severe renal impairment (glomerular filtration rate <30 ml/min/1.73 m^2^ calculated by the Modification of Diet in Renal Disease formula)
Uncontrolled arterial hypertension (SBP >180 mm Hg or DBP >110 mm Hg)
SBP <100 mm Hg at baseline or clinical signs or symptoms of hypotension
Myocardial disease, such as infiltrative myocardial disease (i. e. amyloidosis, hypertrophic cardiomyopathy)
Severe aortic or mitral stenosis or regurgitation or any valvular stenosis or regurgitation with indications for surgery
Coronary artery disease with angina of Canadian Cardiovascular Society class III or IV or requiring nitrates
Unstable angina or acute myocardial infarction <90 days before randomization
Reperfusion procedure (PCI or coronary artery bypass graft) <90 days prior to randomization or <3 weeks in case of a negative stress test after PCI
Stroke with persistent neurological deficits or known hemodynamically relevant symptomatic carotid artery stenosis
Resting heart rate while awake of <50 BPM or >105 BPM or in the case of AF >110 BPM

*IV* indicates intravenous, *ERAs* endothelin receptor antagonists, *PDE-5* phosphodiesterase-5, *COPD* chronic obstructive pulmonary disease, *FEV*
_1_ forced expiratory volume in 1 s, *TLC* total lung capacity, *O*
_2_ oxygen, *AST* aspartate transaminase, *SBP* systolic blood pressure, *DBP* diastolic blood pressure, *PCI* percutaneous coronary intervention, *BPM* beats per minute, *AF* atrial fibrillation

## Study objectives

The primary objective of this study is to assess the pharmacodynamic profile of riociguat in subjects with symptomatic PH-HFPEF. The secondary objectives of this study are to assess changes in dimensions of left and right ventricles and cardiac function parameters using cardiac magnetic resonance imaging (CMRI). Patients with a PVR above and below 240 dyn × s × cm^−5^ will be analyzed as prespecified subgroups.

## Primary efficacy variable

The primary efficacy variable is the change from baseline of cardiac output (CO) at rest, measured by RHC after 26 weeks of study drug treatment.

## Secondary efficacy variables

Change from baseline in left and right atrial area, right ventricular volume and right ventricular ejection fraction, measured by CMRIChange from baseline in PVR, SVR, TPG and PAWP, measured by RHCChange from baseline in WHO classChange from baseline in serum N‑terminal prohormone B‑type natriuretic peptide (NTproBNP) levels

## Exploratory efficacy variables

Change from baseline in all other CMRI parameters not listed above. At selected sites only: T1 mapping and extracellular volume (ECV).Change from baseline in all other RHC parameters not listed under secondary variables.Change from baseline in echocardiography parameters, including left ventricular end-diastolic and end-systolic volumes, tricuspid annular plan systolic excursion, pressure gradient of tricuspid valve, diameter of inferior vena cava, respiratory collapsibility of inferior vena cava, mitral peak velocity of early (E) and late (A) filling, E‑wave deceleration time, LVEF, estimate of mean right atrial pressure, systolic pulmonary artery pressure and E/A ratio.Change from baseline in exercise capacity (6 min walk distance) and in Borg CR 10 scale.Change from baseline in quality of life scores EuroQol five dimensions questionnaire (EQ-5D), MLHF.Events of special interest considered for calculation of the combined endpoint time to clinical worsening.All-cause mortality.Composite endpoint as defined by time to death from cardiovascular causes or first hospitalization for a cardiovascular event, including acute or worsening heart failure, acute myocardial infarction, stroke or ventricular arrhythmia.Change in glomerular filtration rate.

## Pharmacokinetics

To investigate drug exposure and potential relationships to drug effects, plasma concentrations of riociguat and its main metabolite M‑1 (BAY 60-4552) will be determined. Plasma concentrations will be measured using a validated high performance liquid chromatography-mass spectrometry/tandem mass spectrometry (HPLC-MS/MS) method. Quality control (QC) and calibration samples will be analyzed concurrently with study samples. The results of QC samples will be reported together with concentrations in unknown samples in the clinical study report.

## Statistical considerations

Statistical analyses will be performed using Statistical Analysis Software (SAS®). A randomized subject will be valid for safety analysis if at least one dose of study drug was administered. A subject will be part of the full analysis set (FAS) in accordance to the International Conference on Harmonization (ICH) E9 guideline, if he/she belongs to the safety set, is not violating any major entry criteria and shows any postbaseline efficacy data. A subject will be valid for the per-protocol analysis if the subject belongs to FAS and does not show any major protocol deviations that interfere with the interpretation of efficacy results. All variables will be analyzed descriptively with appropriate statistical methods: categorical variables by frequency tables and continuous variables by sample statistics (e.g. number of non-missing data, mean, standard deviation, minimum, median, quartiles and maximum).

The primary efficacy variable will be submitted to an analysis of covariance (ANCOVA) model including the baseline value as covariate, center, treatment regimen and the interaction term of center by treatment regimen as fixed effects. If the treatment-center interaction is not significant at the 0.2 level, the interaction term will be removed from the model for final analysis. The primary comparison will be a one-sided test at the 2.5 % significance level for the difference in treatment effects between riociguat and placebo.

Continuous secondary endpoints will be analyzed in the same manner as the primary endpoint. The change of WHO class will be dichotomized by defining the groups: “improvement by at least one class”, “no improvement by at least one class” and analyzed using Mantel-Haenszel weights stratified by center. The secondary efficacy variables will be tested in exploratory manner at nominal one-sided significance level of 2.5 %.

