### Determination of sample size

Requiring an 80 % power of the trial to detect a mean difference of at least 0.6 l/min between riociguat and placebo with regard to the primary endpoint and assuming a standard deviation of 1.0 l/min, which is derived from a previous trial (LEPHT), then 45 evaluable subjects are needed in each of the 2 treatment groups. Taking into account a drop-out rate of 20 %, a total of 114 subjects are to be randomized (57 subjects per group).

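### A pretest at the 0.2 level decides whether center-by-treatment stays in the primary ANCOVA, so the 2.5% level is not guaranteed and the quantity estimated can change by chance.

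*Protocol article*

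**What the plan says.** The protocol article, under Statistical considerations, analyzes the primary variable (change in resting cardiac output at 26 weeks) by an ANCOVA "including the baseline value as covariate, center, treatment regimen and the interaction term of center by treatment regimen as fixed effects". The next sentence makes the final model depend on a test: "If the treatment-center interaction is not significant at the 0.2 level, the interaction term will be removed from the model for final analysis". The level is then stated without any allowance for that step: "The primary comparison will be a one-sided test at the 2.5 % significance level for the difference in treatment effects".

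The rule carries over to other outcomes: "Continuous secondary endpoints will be analyzed in the same manner as the primary endpoint". The same section says that the secondary variables are tested in an exploratory way at a nominal level.

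Under Determination of sample size, a difference of 0.6 l/min, a standard deviation of 1.0 l/min and 80% power lead to the statement that "45 evaluable subjects are needed in each of the 2 treatment groups". With 20% drop-out this becomes 57 randomized per group, 114 in all.

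The article calls the trial multicenter. It does not give the number or size of centers, say how center-specific effects are weighted if the interaction is kept, or give a rule for pooling small centers. An article may leave such details to the full protocol or SAP, and their absence is not the point here. The pretest itself is stated.

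**The concern.** A test at the 0.2 level on the trial's own outcome decides which model gives the primary result. Even if riociguat works identically everywhere, the interaction is kept in about one trial in five.

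The two models need not estimate the same thing. Without the interaction, the treatment coefficient is a common effect in which larger centers carry more weight. With it, the usual least-squares contrast is the plain average of the center-specific differences, so a center with a few patients counts as much as the largest.

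Three things are at stake: the level of the primary test, the power the sample size was meant to give, and whether an overall effect can be estimated at all if some center has patients in only one arm.

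**Working it through.** **Inputs from the article.** Difference 0.6 l/min, SD 1.0 l/min, one-sided alpha 0.025, power 80%, 45 evaluable per group, drop-out 20%, pretest level 0.2.

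**Assumptions.** Number and sizes of centers; equal weighting of centers when the interaction is kept; no true interaction unless stated; residual SD 1.0.

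**1. The plan's own sample size.** The normal approximation is n = 2 × (1.960 + 0.842)² × 1.0² / 0.6² = 2 × 7.85 / 0.36 = 43.6, so 44 per group. The two-sample t-test needs 44.6, so 45, with 80.4% power at 45. Drop-out: 45 / 0.8 = 56.25, so 57 per group and 114 in total. The stated figures reproduce. They contain no center or interaction term.

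**2. How often the model switches.** With no true interaction the pretest is significant with probability 0.2, so the term is kept in about 20% of trials.

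**3. What the switch does to precision.** With n_k evaluable per arm in center k and K centers:
- common effect: variance = 2 / Σn_k = 2/45 = 0.0444, SE 0.211;
- equal-weight average: variance = (1/K²) × Σ(2/n_k).

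Take an assumed layout of four centers with 33, 6, 4 and 2 per arm. Then Σ(1/n_k) = 0.030 + 0.167 + 0.250 + 0.500 = 0.947, and the variance is 2 × 0.947 / 16 = 0.118, SE 0.344. The SE ratio is 0.344 / 0.211 = 1.63. With equal centers the two variances coincide and the ratio is 1.

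**4. Why the level moves.** The equal-weight average equals the common-effect estimate plus a combination of the interaction contrasts. In the layout above, that second part makes up (0.118 − 0.044) / 0.118, or about 62%, of its variance. Selecting trials with a large interaction F selects trials in which this part is large, so rejections become too frequent.

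Chance-small residual variance in the kept trials plays only a minor part. In uneven layouts of 6 and 8 centers (2 to 20 per arm) the error rate given that the term was kept was 4.7-5.2%. It was still 4.2-4.7% with the variance treated as known. With equal centers, where only the variance mechanism acts, it was about 2.9%.

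**5. Simulated results for the written rule** (90 evaluable patients, no true interaction; power at 0.6 l/min):

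| Assumed layout | Weighting if kept | One-sided type I error | Power, rule | Power, main-effects model |
|---|---|---|---|---|
| Equal, 2-20 centers | equal | 2.5-2.7% | 79-80% | no loss against it |
| Geometric sizes, 2-5 centers, almost no empty cells | equal | 2.6-2.9% | 77-79% | loss about 0.4-3 points |
| Uneven, 6 and 8 centers, no empty cells | equal | 3.0-3.1% | about 76% | 80% |
| Same 6 and 8 centers | by size | 2.6-2.7% | 80-81% | 80% |
| Strongly uneven, 4-10 centers, smallest with 1-2 per arm | equal | 3.1-3.5% | 73-74% | 80% |

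In the last row the interaction model used alone has only 40-50% power. The main-effects model had a simulated type I error of 2.46-2.55% in the layouts run.

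**6. Estimability.** If one arm is empty in a center and the term is kept, the equal-weight difference cannot be estimated. With 8-20 centers of geometric sizes and no pooling, this happened in 10-19% of simulated trials. If those count as non-rejections, power is 63-69% against 78-79%, and type I error is 2.1-2.5%.

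**The case against.** The strongest reply is that most of the harm comes from an assumption the article does not make. It nowhere says that centers are equally weighted. With size-based weights and the same pretest, power is not reduced and the level excess is only about 0.1-0.2 points. Weighting and pooling of small centers are ordinary SAP content, and non-estimability needs a one-arm center, no pooling and the term kept. This stands, and it limits the claim about size. It does not remove the pretest, which any SAP following this sentence would inherit.

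Second, a reader might infer that the primary test has neither its stated 2.5% level nor its stated 80% power. The document does not support so flat a statement. With equal centers the level is 2.5-2.7% and no power is lost. Baseline adjustment may also add power. If baseline correlates 0.3-0.5 with the change (assumed), the residual SD falls to √(1 − 0.3²) = 0.95 or √(1 − 0.5²) = 0.87, and 45 per group gives about 84-90%. That gain is open to the main-effects model too, so it does not argue for the pretest.

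Third, the rule is fixed in advance and leaves the analyst no discretion. The trial is phase IIb with a surrogate endpoint, and the secondary endpoints are exploratory, so no error guarantee is lost for them. All of this bears on severity. What remains for the secondary endpoints is that the quantity estimated may differ from one to the next by chance.

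**Conclusion.** The concern holds in a limited form. It is certain that the primary model is chosen by a pretest on the same data, and that about 20% of trials without a true interaction keep the term. Under equal weighting, this also changes what is estimated.

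The size of the consequence rests on assumptions. Under equal weighting the level is about 2.5-2.7% with equal centers and about 2.6-3.5% with uneven ones. Power is unchanged with equal centers, drops about 0.4-4 points with moderately uneven centers and 5-7 points with strongly uneven ones. Non-estimability is possible, but the document gives no basis for calling it likely. Under size-based weights almost no harm to level or power remains. The sample size calculation is correct for the two-group comparison it describes.

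Severity: should be fixed. The inflation is modest, but the rule governs the primary test. In the layouts run without a true interaction, it brought no material gain over a fixed main-effects model.

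**What to change.** Specify the primary model in advance as ANCOVA with baseline cardiac output, center and treatment, with no interaction term and no pretest. Report the interaction test and center-specific estimates as supportive analyses. Use the same model for the continuous secondary endpoints, which stay exploratory.

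In the simulated layouts this model held 2.46-2.55% type I error and 78-80% power, and its treatment effect stays estimable when a center has only one arm represented. It also fits the two-group sample size calculation better.

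One limit should be acknowledged. If true effects vary between centers (SD 0.3 l/min assumed), the pretest keeps the term in 28-38% of trials, and the main-effects model also exceeds 2.5% as a test of the average effect. The change does not cure that, but it stops a pretest from deciding what is estimated.

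The cost is one sentence of protocol or SAP wording, to be settled before unblinding, with no extra patients or data.

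### The uniform ANCOVA of untransformed change is a poor choice for NT-proBNP: if the marker is strongly right-skewed, power is lost and a few high values dominate the result

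*Protocol article*

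**What the plan says.** The Statistical considerations section prescribes for the primary variable an "analysis of covariance (ANCOVA) model including the baseline value as covariate, center, treatment regimen", plus a center-by-treatment interaction that is dropped if not significant at the 0.2 level. The response is a change on the natural scale: "The primary efficacy variable is the change from baseline of cardiac output (CO) at rest". The same section then extends the method: "Continuous secondary endpoints will be analyzed in the same manner as the primary endpoint". The Secondary efficacy variables section lists, as changes from baseline, serum "natriuretic peptide (NTproBNP) levels" and, from right heart catheterization, the "baseline in PVR, SVR, TPG and PAWP" measures.

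No logarithm, ratio to baseline, rank method or distributional check is mentioned for any of them. WHO class, by contrast, is given its own method directly after the uniform rule. Medians and quartiles are planned as descriptive statistics only. On the status of these tests the section says: "The secondary efficacy variables will be tested in exploratory manner", at a nominal one-sided 2.5%.

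**The concern.** Natriuretic peptide levels tend to span a wide range, and changes in them tend to be proportional to the level. The entry criteria favour a wide spread here: WHO class II to IV, glomerular filtration rate down to 30 ml/min/1.73 m², and atrial fibrillation allowed. If the values are right-skewed and effects multiplicative, an ANCOVA of raw change gives most of its weight to the few patients with the highest values. A clear proportional reduction could then be missed, or the estimate could rest on a handful of people. A mean absolute difference across patients with very different levels is also hard to interpret. The Conclusion presents the trial as groundwork for a phase III study, so an inefficient biomarker estimate has a cost even when its test is only exploratory.

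**Working it through.** **1. The plan's own figure.** The only power calculation is for cardiac output: difference 0.6 l/min, SD 1.0 l/min, one-sided 2.5%, power 80%.

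- Normal approximation: n = 2 × (1.960 + 0.842)² × 1.0² / 0.6² = 43.6, so 44 per group.
- Noncentral t: power 0.795 at 44 and 0.804 at 45, so 45 per group.
- Drop-out of 20%: 45 / 0.80 = 56.25, so 57 per group and 114 in total.

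The stated figures reproduce, and nothing below changes them.

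**2. Inputs for NT-proBNP.** From the article: 45 evaluable per group, one-sided 2.5%, baseline as covariate. Assumed, because the article gives no values: lognormal levels, log-SD (σ) 0.8 to 1.2, log-scale correlation between baseline and week 26 (r) 0.6 to 0.9, and a multiplicative treatment effect. Center terms were left out of both models.

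**3. Log-scale power by formula.** Power ≈ Φ( |ln(ratio)| / [σ√(1 − r²) × √(2/45)] − 1.96 ). For σ = 1.0, r = 0.8 and a ratio of 0.70 this is 0.357 / (0.6 × 0.211) = 2.82, and Φ(2.82 − 1.96) = 0.80. Simulation with the t-test and the covariate gives 79%.

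**4. Simulated power at fixed effects.**

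| log-SD | r | true reduction | raw change | log scale | loss (points) |
|---|---|---|---|---|---|
| 0.8 | 0.8 | 30% | 78% | 93% | 15 |
| 1.0 | 0.8 | 30% | 51% | 79% | 28 |
| 1.2 | 0.8 | 30% | 32% | 64% | 32 |
| 1.2 | 0.7 | 25% | 18% | 35% | 17 |

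**5. Effect set so that the log-scale ANCOVA has about 79% power** (20,000 trials per scenario). Power of the raw-change ANCOVA:

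| log-SD | r = 0.6 | r = 0.75 | r = 0.9 |
|---|---|---|---|
| 0.8 | 62% | 60% | 57% |
| 1.0 | 54% | 52% | 48% |
| 1.2 | 47% | 44% | 41% |

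The loss runs from 16 points (78.5 − 62.0 = 16.5) to 38 points (78.7 − 40.5 = 38.2). Where the log analysis is itself weak or near its ceiling the gap can be slightly smaller. With a 25% reduction it is 15% against 29% (log-SD 1.2, r 0.6) and 84% against 97% (log-SD 0.8, r 0.9).

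**6. Loss expressed as sample.** The efficiency ratio is [(1.96 + z_raw) / (1.96 + z_log)]², where z is the normal quantile of the power. At r = 0.75:

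- log-SD 0.8: [(1.96 + 0.25) / (1.96 + 0.79)]² = 0.65.
- log-SD 1.2: [(1.96 − 0.16) / (1.96 + 0.79)]² = 0.43.

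The raw analysis therefore works as if only about 43% to 65% of the patients were used.

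**7. Dominance of a few values.** At log-SD 1.0, r 0.8 and a 30% reduction, the five largest of the 90 residuals carry a median 63% of the residual sum of squares on the raw scale, against 29% on the log scale.

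**8. Type I error.** With no effect, the raw analysis rejects in 2.0% to 2.6% of trials at the nominal 2.5%.

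**9. PVR and SVR by the same method.** At an assumed log-SD of 0.5 (PVR) raw power is 70% to 71% against 79%, a loss of about 7 to 9 points. At 0.25 to 0.35 (SVR) it is 75% to 77% against 79%, a loss of about 2 to 4 points.

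**The case against.** The strongest objection is that the article is a condensed text and that the scale of analysis is usually settled in the statistical analysis plan, which is not shown. The uniform rule names a model and never says the response must be untransformed. This stands in part: the analysis plan may already specify a logarithm. But the article does not leave the point open. It states one method for all continuous secondary variables, defines the response as a change from baseline, and makes an exception for WHO class but none for NT-proBNP. An analysis plan using logarithms would depart from the rule as published, and the two would need aligning.

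Second, the size is conditional. The article gives no SD, skewness, correlation or expected effect for NT-proBNP, and the simulation draws data from the model under which the log analysis is correct. It shows the cost if the marker behaves that way and does not show that it does. This stands, and it is why a range is given.

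Third, a reader might extend the point to PVR and SVR, which fall under the same rule. The documents do not support that. Under plausible assumed spreads the losses are small, and a log analysis of PVR can fail. Eligibility requires mean pulmonary artery pressure of at least 25 mm Hg and wedge pressure above 15 mm Hg, with no minimum gradient between them. A patient with 25 mm Hg for both would qualify with a gradient of 25 − 25 = 0, and log PVR would be undefined. The article also uses PVR on its natural scale for the subgroup cut at 240 dyn × s × cm⁻⁵.

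**Conclusion.** The point holds for NT-proBNP. As written, the plan analyses its untransformed change. If levels are strongly right-skewed and effects proportional (log-SD 0.8 to 1.2, correlation 0.6 to 0.9, all assumed), this loses roughly 15 to 38 percentage points of power against a log-scale ANCOVA and leaves the result to a few high values.

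A reader might infer that the planned test is invalid or that the trial's main result is at risk. Neither follows. Type I error is not inflated, the sample size concerns cardiac output only, and the secondary variables are exploratory, with no success criterion resting on them. It is a worthwhile improvement to one secondary analysis. That the rule reads as untransformed change is well supported; the size of the loss is only as firm as the assumed spread.

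**What to change.** Except NT-proBNP from the uniform rule. Analyse log(NT-proBNP) at week 26 by ANCOVA with log baseline as covariate and the other terms of the primary model unchanged. Report the riociguat-to-placebo ratio of geometric means with 95% CI, and keep raw-scale summaries as descriptive. If the statistical analysis plan already does this, a sentence reconciling it with the published rule is enough.

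Leave the main analyses of PVR and SVR as they are. If skewness is a worry there, prespecify a sensitivity analysis. For PVR a rank-based one avoids the problem of zero or negative gradients.

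The cost is a sentence or two in the analysis plan, settled before unblinding, with no new data. The small downside is that the NT-proBNP effect is expressed as a ratio and no longer as an absolute difference.
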